### Secondary analyses

Secondary analyses will include further ANCOVAs for each mental health and work related health variable. Baseline scores for the respective independent outcome will be included as a covariate to control for potential baseline differences.

### Further analyses

#### Mediation analysis

To assess the mediating role of proposed variables for the intervention’s effects on work-related rumination, mediation analysis will be performed [120]. As Holidaily encourages users to engage in recreational activities, these may have increased 2 weeks after vacation among those in the IG. To attain temporal precedence, the change in reactional activities will be calculated (post-vacation minus pre-vacation scores). An indirect effect is considered significant if its 95% confidence interval excludes zero.

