**Primary outcome**						
Work-related rumination						
*Work-related rumination (IS)*	✔	✔	✔	✔	✔	✔
*- cognitive irritation*						

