**Potential mediator and moderator**						
Mediator						
Health behaviour						
*Recreational activities (REAQ)*	✔				✔	✔
Moderator						
Technical aspects						
*User experience (AttrakDiff2)*					✔	✔

^a^ only intervention group

All procedures were approved by the ethics committee of Leuphana University in Lueneburg (reference number: 201606, EB-Antrag [name]201606_holidaily). The trial is registered with the German Clinical Trial Register (DRKS00013650).

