### Potential mediator, moderator

#### Mediator

##### Health behaviour: Recreational activities.

The frequency of participants’ engagement in recreational activities after work during the past week is assessed using 21 items from the Recreation Experience and Activity Questionnaire (ReaQ) [111]. Items are rated on a 5-point Likert scale (range 0–4) and have an internal consistency of ﻿*α* = 0.88 [61].

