### Primary analysis

The primary analysis will evaluate the efficacy of Holidaily. The primary endpoint is the difference in work-related rumination, assessed using the irritation score, between the IG and CG 2 weeks after the vacation. We will use analysis of covariance (ANCOVA) to investigate differences in the primary outcome between the two groups, as simulation studies have demonstrated that ANCOVA is the most robust method for analysing RCT’s, in terms of protecting against bias, while enhancing precision and statistical power [117, 118]. Baseline scores for the primary outcome will be included as a covariate. In addition, for the analyses of differences in work-related rumination at the end of the last work day, mid-vacation and at the end of the first work day Bonferroni-Holm corrections will be used to reduce the chances of chance capitalisation [119].

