## Discussion

### Study objectives

This study protocol describes a randomised control trial (RCT) examining the efficacy of a newly-developed behaviour change smartphone app, called Holidaily. Holidaily encourages workers to engage in recreational activities before, during and especially after vacations to ideally prolong the beneficial effects of vacationing. We expect levels of the primary outcome, work-related rumination, to be significantly lower 2 weeks post vacation in the intervention versus waitlist-control group. This finding would be important, especially because the constant mental representation of stressors, despite their absence, has been found to extend stress-related physiological activation and, thereby, contribute to the development and maintenance of mental illness. In addition, the hypothesised mechanism — that a change in recreational behaviour causes the effect on work-related rumination — will be investigated via mediation analysis.

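### The post-minus-pre change score cannot give the mediation analysis temporal precedence, because the mediator is complete only at T5, where the outcome is also measured

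*Protocol article*

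**What the plan says.** The Mediation analysis section (under Further analyses) takes recreational activity as the mediator of the app's effect on work-related rumination. It expects that "these may have increased 2 weeks after vacation among those in the IG", and defines the mediator with this reason: "To attain temporal precedence, the change in reactional activities will be calculated (post-vacation minus pre-vacation scores". Mediation is declared when the 95% confidence interval of the indirect effect excludes zero.

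Table 1 schedules the REAQ at T1, T5 and T6, and marks T6 as intervention group only. The cognitive irritation scale, which carries the primary outcome, is scheduled at every time point. Primary analysis fixes the effect at T5: "The primary endpoint is the difference in work-related rumination, assessed using the irritation score, between the IG and CG 2 weeks after the vacation".

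On recall, the mediator's description says that "engagement in recreational activities after work during the past week is assessed". For all other questions, the introduction to the outcome measures sets the previous week as the default unless another period is clearly stated. The description of the Irritation Scale states none.

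The Discussion (Study objectives) gives as the hypothesised mechanism "that a change in recreational behaviour causes the effect on work-related rumination", to be investigated by this analysis. Explorative hypotheses labels the analysis explorative.

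**The concern.** Temporal precedence means that the mediator is observed before the outcome it is supposed to produce. A difference between two scores is known only when the later score is taken. If that later score comes from the same assessment as the outcome, the lag is zero whatever is subtracted from it.

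The alternative explanation is a natural one here: people who ruminate less about work may do more with their evenings. The app could then lower rumination by some other route, activity would rise as a consequence, and the planned model would show an indirect effect through activity. A reader told that precedence had been secured would have no reason to consider this. At stake is the interpretation of the mechanism, which the Discussion lists among the study's contributions.

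**Working it through.** **Timing, from the protocol's own schedule**

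| Assessment | REAQ (mediator) | Irritation Scale (outcome) |
|---|---|---|
| T1, two weeks before vacation | both arms | both arms |
| T2, T3, T4 | not taken | both arms |
| T5, two weeks after vacation | both arms | both arms; primary endpoint |
| T6, four weeks after vacation | intervention group only | intervention group only |

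1. A two-arm post-minus-pre REAQ score can only be T5 minus T1.
2. The Mediation analysis section does not name the outcome time point. T5 is the one that fits: the intervention effect is defined there, and T6 has no control group.
3. The lag between completed mediator and outcome is T5 - T5 = 0.
4. Precedence would need either a two-arm REAQ score after T1 and before T5, or a two-arm outcome after T5. Table 1 has neither.

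**The sample size, for reference.** For d = 0.20, two-sided 5% level, 80% power and 1:1 allocation, the noncentral t calculation gives 394 per arm, 2 × 394 = 788 in total (power 0.8006). The stated N reproduces and is used below. It has no bearing on the timing.

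**Illustration of the consequence.** Inputs from the protocol: N = 788, d = 0.20, and the rule that the 95% interval excludes zero. Inputs that are assumptions, not in the documents: unit variances, the reverse correlation r between rumination and activity, and a T1-T5 stability of 0.5.

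Simplest model, without baseline: rumination Y = -d × arm + error, and activity M = r × Y + error. Activity has no effect on Y.

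- Path a (arm to M) = r × (-d).
- Path b (M to Y, given arm) = r.
- Spurious indirect effect = a × b = -r² × d, a share r² of the total effect.
- At r = -0.4: -0.16 × 0.20 = -0.032, or 16% of the total.
- At r = -0.1: -0.01 × 0.20 = -0.002, or 1% of the total.

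Share of simulated trials in which mediation is declared, at d = 0.20:

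| Assumed r | T5 score only | T5 minus T1, adjusted for T1 rumination |
|---|---|---|
| -0.1 | 4% | 5% |
| -0.2 | 11% | 8% |
| -0.3 | 15% | 15% |
| -0.4 | 20% | 21% |

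These rates rest on 1,000 simulated trials per setting, so differences of a few points between the columns are noise. The columns agree: taking the change from T1 neither removes nor reduces the false signal.

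**The case against.** The strongest defence is that the analysis is modest by design. Explorative hypotheses calls it explorative and hedges the mechanism. The causal phrase in Study objectives describes a hypothesis to be examined. Limitations reserves strong conclusions for the primary outcome. All of this stands. A reader might infer that the plan commits itself to announcing a causal mechanism; the documents do not support that.

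Second, the change since T1 must have happened before T5, so in that sense it comes first. The change in rumination since T1 also happened before T5, so this orders nothing.

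Third, the shared recall week is stated for the REAQ but only inferred for the Irritation Scale, from the default rule. That is correct. The point does not depend on it, since collection at the same assessment is enough.

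Fourth, the simulated rates depend on a correlation that the documents do not give. At -0.1 the rate is no higher than a nominal 5%. Much higher rates can be produced, for example about 63% at r = -0.4 and d = 0.40, but that doubles the effect on which the trial is sized. A reader should not take any of these figures as this trial's error rate.

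Finally, an analysis plan not shown here may give more detail on the model. It could not create a two-arm activity score that the schedule does not collect.

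**Conclusion.** The statement that the change score attains temporal precedence is wrong on the protocol's own schedule. This rests on Table 1 and the definition of the primary endpoint, and needs no assumption beyond taking T5 as the outcome time for the mediation model. The planned rule cannot separate activity lowering rumination from lower rumination raising activity.

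The size of the resulting error is not known. On the stated assumptions it runs from negligible to about one declared mediation in five at d = 0.20, with a spurious share of the total effect of about 1% to 16%.

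The consequence is confined to the interpretation of one explorative analysis. A reader might infer that the efficacy result is also in doubt; it is not, because the primary endpoint, the sample size and the primary ANCOVA do not use the mediator.

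**What to change.** In Mediation analysis, delete the clause claiming temporal precedence. State that the T5 recreational-activity model is explorative and describes a concurrent association, which does not establish the direction of the effect. Carry the same wording into the report. The cost is a sentence; no data or analysis changes.

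Optionally, add a supplementary analysis of a different mediator that does precede the outcome: the relaxation subscale of the DRAMMA-Q, which Table 1 collects in both arms at T2, T3 and T4. Fix one of these time points in advance, with T5 rumination as outcome and T1 relaxation and T1 rumination as covariates. The data are already scheduled, so the cost is analysis time.

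The detachment subscale should not be used for this. The Background section on mental detachment reports a high overlap between it and rumination, and the primary scale itself is described as assessing the ability to detach, so it would come close to the outcome predicting itself.

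The supplementary analysis has limits that should be stated with it. It supplies temporal order but does not remove confounding. It does not test how often people engage in recreational activities. With a one-week recall, scores at T3 and T4 largely describe the vacation, not the return to work.

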### Mental detachment

While work-related rumination increases the risk of acute stressors developing into chronic load reactions and adverse health, mental detachment has been found to buffer this relationship. Mentally disengaging and experiencing a “sense of being away” ([33], p. 579) from work during leisure time describes the process of mental detachment [34]. Although several recovery experiences are important, mental detachment has received the most research attention and been found to be particularly vital for the recovery process [12]. Among others, the Stressor-Detachment Model [35] and DRAMMA Model [36] concordantly emphasise the central role of mental detachment in protecting workers from chronic load reactions. Results from several meta-analysis indicate that mental detachment is strongly related to health indicators like depression, burnout, sleep complaints, ﻿and general wellbeing [18]. They also indicate a positive relationship between mental detachment and state of recovery amongst workers [12]. Moreover, the influence of mental detachment does not seem limited to worker health and recovery. It also can affect workers’ creativity [37, 38]. Similar associations between both work-related rumination and the lack of mental detachment and health outcomes might be explained by findings that suggest a high degree of overlap between work-related rumination and (lower levels of) mental detachment [39]. Despite the importance of mental detachment, workers who experience severe forms of occupational stress struggle, especially to mentally disengage or “switch off” from work, despite their increased need to recover [40].

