**Other variables**						
Work characteristics						
*Unfinished tasks*	✔	✔		✔	✔	
*Time pressure (ISTA)*	✔	✔		✔	✔	
*Work availability during vacation*	✔			✔	✔	
*Working overtime*	✔					
*Task variety (WDQ)*	✔					
*Social support at work (SzSU)*	✔					
Personal characteristics						
*Work engagement (UWES)*	✔	✔		✔	✔	✔
*Work performance (OCB)*	✔	✔		✔	✔	
*Boundary management (WLI)*	✔					
*Work-Life-Balance (TKS-WLB)*	✔	✔			✔	✔
*Life-satisfaction (SWLS)*	✔					
*Resilience (RS)*	✔				✔	
*Vitality (PANAS)*	✔	✔	✔	✔	✔	✔
*Physical health*	✔					
*Wellbeing*	✔	✔	✔	✔	✔	
*Need for recovery (NFR)*	✔	✔		✔		✔
*Creativity (objective) (TTCT)*	✔	✔		✔		
*Creativity (subjective)*	✔	✔		✔	✔	

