Third, findings from previous observational studies suggest that the beneficial vacation effect experienced by workers is not sustained, but fades out shortly after they return to work, with mental health indicators returning to pre-vacation levels [46, 47, 56]. Consistent with previous investigators, who usually selected 2 weeks to describe the fading effect, we maintained this timeframe for our primary measurement. Additionally, a 2 week extended follow-up also is included, albeit only to assess stabilisation after the vacation in the intervention group. Further investigations are, therefore, needed. While 2 weeks may be insufficient to verify lasting behavioural changes, they might provide insights into whether the fadeout effect can be reduced. If Holidaily appears to be effective in the short-term only, future studies should also consider potential facilitators and barriers for long-term maintenance.

In the present study, three possible barriers might limit the intervention’s effect to two-weeks. For instance, after their vacation, workers may experience reduced motivation and increased effort to engage in recovery behaviours, due to stresses encountered at work (e.g., work accumulation during their absence; see also [57]). This might lead to an initial relapse, prompting the fading of the beneficial effect. To overcome such barriers, certain behavioural change techniques, like prompts and self-monitoring, were integrated into this intervention to promote engagement in recovery behaviours during daily working life. It is unclear whether these are appropriate strategies, however. To assess changes and control for potential confounders, for instance, workers’ motivation/engagement is being measured by the Utrecht Work Engagement Scale [95]

Second, the length of workers’ vacation may play a greater role determining the maintenance of behavioural change than previously anticipated. In one study, as few as 18 or as many as 254 days are required before a newly adopted health behaviour — like improved diet or regular exercise — becomes stable and replaces previously dominant behaviours [126]. Contrastingly, workers in Germany are legally entitled to a minimum of 24 days of paid vacation. Although the length of workers’ vacation period may be long enough to initiate short-term behavioural change, it might be insufficient for benefits to be maintained long-term. Hence, vacation length will be considered as a confounder.

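### The mediation rule specifies no control for post-return workload, a plausible common cause of activity and rumination, so it can declare an indirect effect when activity does nothing

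*Protocol article*

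**What the plan says.** The Mediation analysis section defines the mediator: "the change in reactional activities will be calculated (post-vacation minus pre-vacation scores"). In Table 1 recreational activities are measured in both arms only at T1 and T5, so the change ends at the visit where the primary outcome is taken. The decision rule is "An indirect effect is considered significant if its 95% confidence interval excludes zero". The section lists no covariates.

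The Discussion (Study objectives) gives the hypothesis under test, namely "that a change in recreational behaviour causes the effect on work-related rumination".

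Three other places bear on workload:

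- Limitations says that after vacation "workers may experience reduced motivation and increased effort to engage in recovery behaviours, due to stresses encountered at work", and gives accumulated work as the example.
- The Background (Mental detachment) says that "workers who experience severe forms of occupational stress struggle, especially to mentally disengage". The section on work-related rumination reports that rumination mediates the relation between work stress and sleep complaints, which presupposes a link from work stress to rumination.
- Table 1 schedules unfinished tasks and "Time pressure (ISTA") at T1, T2, T4 and T5. Vacation specifics adds anticipated work accumulation, asked before departure.

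On confounding, Limitations says "Hence, vacation length will be considered as a confounder" and mentions work engagement as a further example. Workload is not named. The section on secondary outcomes and other variables states that other variables will be used to study mechanism, effect modification and confounders of the primary outcome. It does not connect them to the mediation model.

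**The concern.** An indirect effect is the product of two paths. The path from arm to activity is randomised. The path from activity to rumination is an observational association within arms, and anything that moves both variables biases it. Workload after return is the obvious candidate on the protocol's own account: busy workers may do less after work and ruminate more. Activity and rumination would then be negatively related even if activity had no effect. If the app also raises activity, the product is nonzero and has the hypothesised sign, so the error would look like confirmation.

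The change score does not remove a cause that arises after return. Nor would the covariate rule under Sensitivity analyses catch it, because that rule selects variables on baseline differences between arms. The problem is also separate from the timing of the mediator, since it would remain if activity were measured a week earlier. At stake is a mechanism claim that the Discussion lists among the study's contributions and that could steer later app design.

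**Working it through.** **Inputs from the protocol.** d = 0.20, two-sided 5% level, 80% power, N = 788, 1:1 allocation (Sample size calculation; Procedures). Baseline rumination is a covariate in the primary ANCOVA and is carried into the check.

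**The plan's own figure.** The normal approximation gives n = 2(1.96 + 0.8416)²/0.20² = 392.4, so 393 per arm (786). The exact t-test needs 394 per arm, or 788 in total, with power 80.1%. The stated size reproduces. The mediation analysis has no figure of its own.

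**Assumptions (none is in the documents).** The app raises activity by a = 0.3 SD. Activity has no effect on rumination. Workload lowers activity by u and raises rumination by u, in SD units. Baseline rumination correlates 0.5 with the outcome, and the app's effect of 0.20 SD is wholly direct.

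**Closed form, workload acting on the change score itself.**

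- Spurious activity-to-rumination slope: b = -u².
- Spurious indirect effect: a × b = -0.3u².
- SE(b) ≈ √((0.75 - u⁴)/788), about 0.031.
- SE(a) ≈ 2/√788 = 0.071, so a/SE = 4.2 and the first path is almost always detected.

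At u = 0.1: b = -0.01 and |b|/SE = 0.32, so the b path is significant in about 6% of trials.

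At u = 0.2: b = -0.04 and |b|/SE = 1.30, about 25%. The indirect effect is -0.012 SD, and 0.012/0.20 = 6% of the target effect.

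At u = 0.3: b = -0.09 and |b|/SE = 2.93, about 83%. The indirect effect is -0.027 SD, and 0.027/0.20 = 14% of the target.

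**Simulation of the same set-up** (1,000 trials per cell, Monte Carlo intervals, N = 788, a = 0.3), as the share of trials declaring mediation:

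| u | workload omitted | adjusted, measured without error |
|---|---|---|
| 0 | 5% | 5% |
| 0.1 | 6% | 5% |
| 0.2 | 26% | 5% |
| 0.3 | 84% | 6% |

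A percentile bootstrap (200 trials) gives 28% and 79% at u = 0.2 and 0.3. With 552 analysed (30% loss, assumed) the rates are 19% and 67%. With a = 0 the rate is at most 4% at every u. If the workload measure has reliability 0.7, the adjusted rates are 6% at u = 0.2 and 17% at u = 0.3.

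**Change score built from T1 and T5 activity.** Here strengths are in SD of activity, with stable individual levels. Two simulations with no true activity effect gave the following; a dash means that the setting was not run.

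| workload on activity / rumination | planned model | with T1 and T5 workload |
|---|---|---|
| 0.1 / 0.1 | 6% | 4% |
| 0.2 / 0.3 | 17-20% | 5% |
| 0.3 / 0.3 | 38-42% | 12% |
| 0.3 / 0.4 | 70% | – |
| 0.4 / 0.4 | 76-94% | 22% |

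This set-up is closer to the planned mediator. At 0.3 its rates are lower than the 84% above because the same strength is a smaller share of a noisier change score.

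Adjusting for T1 workload alone does almost nothing. In a related model (T5 activity adjusted for T1 activity) the rates at the four stronger settings went from 32%, 62%, 87% and 99% to 32%, 63%, 89% and 99%.

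**The case against.** The strongest reply is that this is a condensed article, that the mediation analysis is labelled explorative, and that its covariates may properly sit in an analysis plan that is not shown. That holds as far as it goes, and it is why the point concerns one analysis and not the trial. What remains is that the article itself fixes a decision rule, and that its discussion of confounders passes over the work stress it has just named as a barrier.

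Four stronger readings are tempting and not supported.

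- A reader might infer that the workload measures are collected and left unused. The protocol does state a general intent to use other variables for mechanism and confounders. It only fails to attach them to this model.
- A reader might infer that the protocol asserts causation. The causal wording states a hypothesis to be investigated, and Limitations confines strong conclusions to the primary outcome.
- A reader might take it as established that work stress lowers recovery behaviour. The protocol says only that it *may*, and the link from workload to rumination is drawn from the Background.
- A reader might infer that any rise in activity will produce false mediation. At 0.1 SD the rate is near nominal.

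Adjustment for T5 workload is also open to objection. It is self-reported, post-randomisation and taken at the same visit as mediator and outcome. If activity lowers and rumination raises perceived workload (0.3 each, assumed), adjusting for it cut detection of a true activity effect of -0.15 from 64% to 25%, and raised false positives from 6% to 13%. This stands, so T5 adjustment cannot be the only analysis and cannot by itself license a causal claim.

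**Conclusion.** The concern holds for the explorative mediation analysis. As written, the rule can declare an indirect effect that is due to workload after return. With N = 788, a = 0.3 SD and no true activity effect, the false-declaration rate is about nominal at 0.1 SD, roughly 17-42% at 0.2-0.3 SD and 76-94% at 0.4 SD. Under the simpler scaling it reaches 84% at 0.3 SD. Every strength is an assumption, and the error largely disappears if the app does not change activity. Workload adjustment reduces the bias but does not remove it when workload is measured with error. The randomised comparison of rumination at two weeks, and so the efficacy conclusion, is not affected.

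**What to change.** 1. Keep the planned model and report it.
2. Beside it, report a version with time pressure and unfinished tasks at T1 and T4 in both the mediator and the outcome equation. T4 precedes the outcome visit but removes less of the bias, because it captures the first working day and not the following two weeks. The work-characteristics items refer by default to the past seven days, so state which window the T4 items used.
3. Report a separate version with T1 and T5 workload. Note that T5 is post-randomisation, measured at the same visit, and may itself be affected by the app, activity or rumination.
4. State how strong a residual common cause would have to be to bring the indirect effect to zero. On the standardised scale used above, a slope of -0.04 is fully explained by 0.2 × 0.2.
5. Report an association consistent with the hypothesised mechanism, and do not say that activity causes the effect, unless the result survives both the adjusted versions and the sensitivity analysis.

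The cost is a few extra models on data already scheduled and some changed wording. The downside is possible over-adjustment in the T5 version, which is why the versions are shown side by side.
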